### Study population/participants

To include a representative patient group, we will select potential participating couples retrospectively in each clinic by means of the clinics’ financial registration database (Diagnosis Treatment Combination code). In this nationwide registration system, patients undergoing diagnostics or treatment for infertility are identified with a specific fertility code (F-code). For the baseline measurement, we will invite couples that were given the code for new fertility patients (F-11) between February 2011 to March 2012 to participate in this study. For the after measurement, we will invite the couples that were given the F-11 code during the ten- to twelve-month intervention period. We will invite couples to participate by giving their permission for a medical record study and filling out a questionnaire.

The couples are eligible to participate when they have been diagnosed with unexplained or mild infertility, have a good prognosis (>30%) according to Hunault’s prediction model, did not have previous fertility treatment, and the female age is between 18 and 38 years. Couples with bilateral tubal pathology, severe male factor, or anovulation are not eligible to participate.

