### Secondary outcomes effectiveness

1. Treatment-related measures: time to the start of fertility treatment and the number and types of fertility treatments that the couples received.

2. Treatment outcome-related measures: (ongoing) pregnancy rate, miscarriage, extra uterine gravidity, multiple pregnancy rate, and time to pregnancy.

3. Patient-related outcome measures : general experiences with fertility care such as information provision, respect for patients’ values and accessibility of care (to be measured with Patient Centeredness Questionnaire Infertility) [26], specific experiences with the prognostic model and TEM, quality of life (estimated by FertiQoL)[27], and trust in physician (measured by Wake Forest Trust Scale) [28].

4. Process related measures: percentage transition of patients to another fertility center.

5. Background characteristics that could influence guideline adherence (*e.g.*, age, referral status, type of infertility, duration and cause of infertility).

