## Data collection

### Effectiveness

Data collection will be performed from medical records and a patient questionnaire.

Data abstraction from medical records will be performed using a standardized audit form. We will collect the background characteristics, treatment related measures, treatment outcome-related measures, and process-related measures.

The questionnaire will be divided into four parts. The first part consists of background questions (*e.g.*, highest educational level, country of birth). The second part regards the patients’ experience with the prognostic model and TEM as well as the patients’ trust in both the GP as well as the fertility doctor/gynecologist. The third part is the Patient-Centeredness Questionnaire-Infertility, a validated instrument measuring patient-centeredness of fertility care by asking about patients’ experiences with care. The last part is the FertiQol questionnaire, We will only use the Core module, which involves questions about mind-body, emotional, relational, and social aspects.

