### Data analysis

To analyze the effectiveness of the implementation strategy, descriptive statistics and multilevel analysis will be used. The statistical analysis will be performed using SPSS version 16.0 for Windows.

The main outcome, the difference in baseline and after-measurement scores in guideline adherence on TEM, between the intervention and control group will be analyzed with the chi-square test.

Descriptive analysis will be used to assess the difference in treatment-related, treatment outcome-related, and patient-related measurements between the intervention and control group. Furthermore, time to pregnancy and time to start fertility treatment will be analyzed using Kaplan Meier analysis with log-rank test. Univariate and subsequent multivariate logistic and Cox regression analyses will be used to analyze the relative contribution of the implementation strategy versus other predictive factors for guideline adherence on TEM.

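### The main comparison of adherence uses no couple-level covariate, although age is collected and each eligible couple's Hunault probability must be known; pre-specified adjustment would be a small, nearly free improvement.

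*Protocol article*

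**What the plan says.** The Data analysis section of the protocol article defines the contrast as "The main outcome, the difference in baseline and after-measurement scores in guideline adherence on TEM". The same sentence then assigns its test, stating that this contrast "between the intervention and control group will be analyzed with the chi-square test".

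Two other statements in that section bear on adjustment. It opens by saying that for effectiveness "descriptive statistics and multilevel analysis will be used", without linking the multilevel part to the main outcome. It closes with univariate and then multivariate logistic and Cox regression to "analyze the relative contribution of the implementation strategy versus other predictive factors for guideline adherence on TEM".

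On what is available for each couple:

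- Secondary outcomes effectiveness, item 5, is headed "Background characteristics that could influence guideline adherence". Its examples are age, referral status, and type, duration and cause of infertility. Hunault prognosis is not among them.
- Data collection, Effectiveness, on the audit form: "We will collect the background characteristics, treatment related measures, treatment outcome-related measures, and process-related measures".
- Study population/participants makes a Hunault probability above 30% an eligibility criterion, so the value has to be known for each included couple.

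Randomization is stratified for IVF facilities only, and the result is communicated to the clinics. After-wave couples are those registered as new fertility patients during the intervention period that follows.

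**The concern.** The article says couple characteristics may affect adherence and collects them, but the test it names for the main result uses none of them. Couples just above the 30% threshold and couples well above it are all eligible, and they need not be equally ready to wait six months. Only 25 clinics are randomised, with one stratification factor, and each wave is a fresh sample of couples. The case-mix of the arms can therefore drift apart between waves.

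Chance is not the only route. After-wave couples are referred, diagnosed and invited when allocation is known. The strategy includes feedback to GPs on referral, a local protocol on identifying mild or unexplained infertility, and training in the prognostic model. A shift in who enters, in one arm and one wave only, would not be removed by randomisation or by subtracting the baseline. Part of a case-mix difference could then be read as an effect of the strategy, or could mask one.

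**Working it through.** **Inputs from the article (Sample size; Randomization).** 60% v 80% adherence, ICC 0.1, alpha 5%, 25 clinics, 450 couples, 15 to 20 per clinic in each wave. 450/25 = 18 per clinic.

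**The article's own figure.** Power and sidedness are not stated; assume 80% and two-sided. Two proportions of 60% and 80% need 82 per arm without continuity correction. The design effect is 1 + (18 − 1) × 0.1 = 2.7. Total: 2 × 82 × 2.7 = 443, against 450 stated. This reproduces, so 18 per clinic is a fair basis for what follows.

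**Assumptions not in the article.** Split of 12 v 13 clinics (the nearest to equal); within-clinic SD of prognosis 6 to 10 points; adherence rising 0.5 to 1.5 percentage points per prognosis point.

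**Chance imbalance on the change scale.** If each clinic's underlying case-mix is the same in both waves, it cancels, and only the sampling of 18 couples per clinic per wave remains:

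SD of imbalance = sqrt[2 × sdW²/18 × (1/12 + 1/13)], with 1/12 + 1/13 = 0.1603.

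- sdW = 6: sqrt(4.00 × 0.1603) = 0.80 points
- sdW = 10: sqrt(11.11 × 0.1603) = 1.33 points

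Times the slope: 0.80 × 0.5 = 0.4, up to 1.33 × 1.5 = 2.0 percentage points for a 1-SD imbalance.

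**Precision gained by adjusting.** Simulation under no effect, 3,000 trials per setting: 25 clinics (13 v 12), 18 couples per clinic per wave, total ICC about 0.1, clinic correlation between waves 0.8. One standardised covariate has an odds ratio of 1.3 to 2.0 per SD and a clinic-mean SD of 0 to 0.4. SD of the estimated effect, unadjusted to adjusted:

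| Odds ratio per SD, clinic SD | Change from baseline | After wave only |
|---|---|---|
| 1.3, 0 | 0.0709 to 0.0703 | 0.0686 to 0.0684 |
| 1.5, 0.4 | 0.0708 to 0.0698 | 0.0685 to 0.0665 |
| 2.0, 0.4 | 0.0716 to 0.0684 | 0.0675 to 0.0622 |

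Over all nine settings the reduction is 0.6% to 4.5% for the change, which is the contrast the article names, and 0.3% to 7.9% for the after wave alone. The mean estimate stayed within about 0.2 percentage points of zero, so chance imbalance brings no systematic bias.

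**Do the two sets of assumptions agree?** Slope times SD gives 0.5 × 6 = 3 to 1.5 × 10 = 15 percentage points per SD. The odds ratios give, near 60% adherence, 0.24 × ln 1.3 = 6 to 0.24 × ln 2.0 = 17 points per SD. The ranges overlap. Also, a 2.0-point component in an SD of about 7.1 is 2.0²/7.1² = 8% of the variance. Removing it cuts the SD by 1 − sqrt(0.92) = 4%, in line with the simulated upper end for the change.

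**A systematic shift.** The article gives no size. If the arms' change in mean prognosis differed by 3 to 5 points, the effect would move by 3 × 0.5 = 1.5 to 5 × 1.5 = 7.5 percentage points. That is 3/1.33 = 2.3 to 5/0.80 = 6.3 SDs of the chance imbalance above, so it would need a real change in intake.

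**The case against.** The strongest case against has four parts.

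1. *The main outcome is a change.* A reader might infer that any case-mix difference between the arms' clinics passes whole into the effect. It does not, because stable clinic differences cancel. This stands, and the chance figure above is confined to what is left.
2. *Adjustment is already planned.* A multivariate logistic regression containing the strategy and other predictors does give an adjusted effect, and multilevel analysis is named. It would be wrong to say the article has no adjusted analysis. But neither is designated the main result, and the regression is framed as weighing predictors against each other. The chi-square test is a stated choice, so the point does not rest on detail commonly left to an analysis plan.
3. *Little is at stake.* This also stands: the gain is a few per cent of the SD, and under randomisation alone the imbalance is already part of the standard error. The same sentence has a larger and separate problem. A chi-square test that ignores an ICC of 0.1 would have a type I error of about 21% to 25% on after-wave data at 15 to 20 couples per clinic. Correcting for clustering would still leave couple-level case-mix unadjusted.
4. *After-wave prognosis is measured after allocation.* The strategy could alter who is referred or recorded as eligible, and with what prognosis. This is a fair caution. It is a reason to keep the model without these covariates in view. Nor can adjustment repair selection on unmeasured factors.

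**Conclusion.** The point holds as a minor improvement. The test named for the main comparison takes no couple-level covariate, although age and other possible influences are collected and Hunault probability is needed for eligibility. On the assumed inputs a 1-SD chance imbalance moves the effect by 0.4 to 2.0 percentage points against a 20-point target. Adjustment lowers the SD of the estimate by under 1% to about 8%; the upper end belongs to the after-wave contrast, and for the change it is about 4.5%. The slopes, SDs, odds ratios and the 12 v 13 split are all assumptions.

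Three stronger readings are not supported. The article does not list Hunault prognosis as an influence on adherence; it is an eligibility criterion. It does not show that the unadjusted estimate is biased. And the 1.5 to 7.5 point figure is conditional on a differential intake shift for which the article gives no evidence. The main value of adjustment is protection against such a shift in measured characteristics, with a little precision besides.

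**What to change.** Name one main model in Data analysis: a multilevel model for adherence with clinic as the cluster and an arm-by-period term. Include female age and Hunault probability (continuous) as fixed, pre-specified couple-level covariates. Report the arm effect as a standardised difference in percentage adherence, so that it stays on the scale of the primary outcome. Show the same model without the two covariates as a sensitivity analysis, because the strategy could slightly alter who is referred or recorded as eligible. Keep the predictor regression as a separate secondary analysis.

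The cost is a sentence or two and no new data. One practical check is that the audit form stores the Hunault value itself, and not only whether the couple passed the threshold. The Trial status section says the baseline measurement is still running, so the covariates can be fixed before any after-wave data exist.

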## Background

Subfertility is defined as the absence of conception after one year of unprotected intercourse [1]. It affects approximately 9% of all couples of reproductive age [2,3]. In approximately 50% of the couples, no major cause is found after the basic fertility work-up [4]. In those couples, the chance of natural conception can be calculated via validated prognostic models [5,6]. If the chance of natural conception within one year is good, meaning a probability of 30% or more, expectant management for 6 to 12 months is equally effective as treatment [7]. Because this expectant management is restricted to couples with a good prognosis, we have called it tailored expectant management (TEM).

European Society of Reproductive Medicine (ESHRE) and National Institute of Health and Clinical Excellence (NICE) guidelines on the management of infertility both emphasize that couples should not be exposed to unnecessary risks or ineffective treatments and encourage that each subfertile couple should receive information about the estimate of their chance of natural conception [8,9]. In the Netherlands, the national network guideline on infertility for gynecologists and general practitioners (GPs) explicitly recommends the use of prognostic models and subsequent TEM for couples with unexplained or mild infertility [10]. However, at this moment, implementation of TEM is poor. A recent Dutch multicenter cohort study showed overtreatment in 36% of the couples, *i.e.*, 36% of the couples with a good prognosis eligible for TEM (>30% chance of natural conception in one year) already started medically assisted reproduction (MAR) [11].

This overtreatment in subfertile couples is worrisome for several reasons. First, fertility treatment still leads to a considerable number of multiple pregnancies, which are associated with a higher morbidity and mortality in both mothers and neonates [12]. Second, fertility treatment carries a significant physical and psychological burden and accompanying productivity loss [13-16]. Third, fertility treatment and its complications are expensive and put considerable financial strain on societies where MAR is reimbursed or on the subfertile couples in societies where MAR is not or only partially reimbursed [17].

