### Effectiveness

For the effectiveness, a baseline measurement will be performed in all participating clinics, including guideline adherence on TEM, and a range of organizational, professional, and patient characteristics (see outcome measures). Following baseline measurement, the multifaceted implementation strategy will be applied in the intervention clinics. After ten to twelve months of intervention exposure, the after measurement will be performed again in all 25 participating clinics.

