### Professional level (*e.g.*, gynecologists (in training), fertility doctors, and GPs)

The strategy regarding the professionals contains audit and feedback, an education outreach visit, supportive consultation tools, and a video-based communication training.

The audit and feedback of the current care will consist of a feedback report based on the results of the baseline measurement. This feedback will report clinic’s guideline adherence on TEM in a twelve-month period prior to the randomization compared with the other participating clinics. It will give insight in how they are adhering to the guideline concerning the policy for couples with unexplained or mild infertility, *e.g.*, use of prognostic models and subsequent TEM in case the prognosis is good. Furthermore, the report will provide feedback on patient-related measures like general experiences with fertility care, specific experiences with the prognostic model and TEM, quality of life, and trust in their physician [ref].

In addition to this audit and feedback, an educational outreach visit will take place with fertility doctors and gynecologists (in training), in which background information about how and when to use the prognostic model of Hunault, and subsequent TEM will be given and in which the results of the baseline measurement and local barriers will be discussed. The result of this visit will be an individualized action plan per clinic.

The supportive consultation tools are developed containing a digital version of the prognostic model of Hunault on a website and we will provide professionals with a summary of the guideline on TEM in the form of a pocket card.

Finally, a video-based training strategy will be provided to improve the communication techniques to counsel the patients on their chance of spontaneous conception versus conception after treatment, the (dis)advantages of expectant management versus fertility treatment, and on the reason for TEM (*i.e.*, making clear it is not a waste of time). Consistent with functional models of medical communication described in the field [24], the LEAPS Framework, a pneumonic for Listen, Educate, Assess, Partner and Support will be used to develop the intervention [25].

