### Sample size

The expected adherence to TEM in the control arm is estimated based on previous studies at 60% [11]. To increase this to 80% with an intra-class correlation (ICC) of 0.1, alpha at 5%, comparing two strategies, we estimate that with 25 clusters we would need a total sample size of 450 patients. This means we need to include 15 to 20 patients per clinic in the baseline as well as in the after measurement.

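### Secondary outcomes, pregnancy included, are given no cluster-adjusted effect estimate with a confidence interval, and the role of the baseline wave is stated only for adherence

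*Protocol article*

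**What the plan says.** All references are to the protocol article.

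- **Data analysis, secondary outcomes.** "Descriptive analysis will be used to assess the difference in treatment-related, treatment outcome-related, and patient-related measurements between the intervention and control group". The sentence names no wave, estimator or interval. Under Secondary outcomes effectiveness, the treatment outcome-related group contains the pregnancy outcomes.
- **Data analysis, time outcomes.** "time to pregnancy and time to start fertility treatment will be analyzed using Kaplan Meier analysis with log-rank test".
- **Data analysis, other statements.** The section opens by naming multilevel analysis alongside descriptive statistics for effectiveness, without attaching it to any outcome. The contrast of baseline and after measurement is named for the main outcome, adherence. The logistic and Cox regressions are tied to predictors of adherence.
- **Effectiveness.** "a baseline measurement will be performed in all participating clinics, including guideline adherence on TEM, and a range of organizational, professional, and patient characteristics".
- **Professional level.** Intervention clinics receive their baseline results, and "the report will provide feedback on patient-related measures like general experiences with fertility care". So the patient-related measures will exist at baseline.
- **Background.** The rationale is that, for couples with a good prognosis, "expectant management for 6 to 12 months is equally effective as treatment".
- **Sample size.** "The expected adherence to TEM in the control arm is estimated based on previous studies at 60" per cent. The target and the allowance for clustering follow: "To increase this to 80% with an intra-class correlation (ICC) of 0.1, alpha at 5%, comparing two strategies". The result of the calculation is 450 couples in 25 clinics.

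**The concern.** The methods named for the secondary outcomes are weaker than the design requires and allows.

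1. **Clustering.** Clinics are randomised, and the sample size allows for correlation within clinics. An ordinary log-rank test treats couples as independent. If pregnancy or treatment start varies between clinics, its p-value is too small.
2. **No interval for pregnancy.** The strategy aims to make more couples wait, which is a good result only if pregnancies are not lost. The economic ratio is cost per percentage point of adherence, so lost pregnancies do not enter its denominator. The between-arm pregnancy comparison is therefore the main place where harm would show. Neither a descriptive contrast nor a p-value tells the reader how large a loss remains possible.
3. **Baseline wave.** Clinic-level baseline values will exist for at least the patient-related outcomes. With 25 clinics, chance imbalance between arms is likely enough to matter. The article does not say whether these values enter any analysis other than that of adherence.

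**Working it through.** **Inputs from the article:** 60% versus 80% adherence, ICC 0.1, alpha 5%, 25 clinics, 450 couples in each wave. This gives 450/25 = 18 couples per clinic and about 225 per arm.

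**Assumed, because the article does not give them:** 80% power and a two-sided test; a pregnancy rate of 30% to 50% (30% is the eligibility threshold for a good prognosis); an ICC for pregnancy of 0 to 0.1; and a correlation of 0.8 between a clinic's true means in the two waves.

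**Step 1. The plan's own figure.** With pooled variance and no continuity correction:

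n per arm = [1.96 × √(2 × 0.7 × 0.3) + 0.842 × √(0.24 + 0.16)]² / 0.2² = 81.2, rounded up to 82.

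Design effect = 1 + 17 × 0.1 = 2.7. Total = 2 × 82 × 2.7 = 443, against the stated 450. The figure reproduces, and it includes an allowance for clustering.

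**Step 2. Error of a test that ignores clustering.** With design effect D = 1 + 17 × ICC, the true two-sided error of a nominal 5% test is about 2 × [1 − Φ(1.96/√D)].

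| ICC | D | 1.96/√D | True error |
|---|---|---|---|
| 0.02 | 1.34 | 1.69 | about 9% |
| 0.10 | 2.70 | 1.19 | about 23% |

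This is a normal approximation applied to the log-rank statistic. At ICC 0 there is no inflation.

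**Step 3. What an observed pregnancy difference of zero could hide.** The half-width of the 95% interval in the after wave is 1.96 × √(2p(1 − p)/225 × D).

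| Pregnancy rate | ICC 0 | ICC 0.02 | ICC 0.05 | ICC 0.10 |
|---|---|---|---|---|
| 30% | 8.5 | 9.8 | 11.5 | 13.9 |
| 40% | 9.1 | 10.5 | 12.3 | 14.9 |
| 50% | 9.2 | 10.7 | 12.6 | 15.2 |

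Entries are percentage points. The range is 8.5 to 15.2, or about 9 to 15.

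**Step 4. What the baseline wave could add.** The waves contain different couples, so the correlation between a clinic's two observed means is r = 18 × ICC × 0.8 / D. Relative to an after-only comparison, the variance is multiplied by 1 − r² with covariate adjustment and by 2(1 − r) with a plain change from baseline.

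| ICC | r | Adjusted | Plain change |
|---|---|---|---|
| 0 | 0 | 1.00 | 2.00 |
| 0.02 | 0.215 | 0.954 | 1.57 |
| 0.05 | 0.389 | 0.849 | 1.22 |
| 0.10 | 0.533 | 0.716 | 0.93 |

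Adjustment cuts the variance by about 5% at ICC 0.02, 15% at 0.05 and 28% at 0.10. Estimating one clinic-level covariate from 25 clinics costs a factor of about 22/21 = 1.05. The net factors are therefore about 1.00, 0.89 and 0.75. A plain change from baseline loses precision except at the top of the ICC range.

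For pregnancy at a 30% rate, the adjusted half-widths before that cost are 9.6, 10.6 and 11.8 points at ICC 0.02, 0.05 and 0.10. The interval stays wide either way.

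**The case against.** The strongest reply is that this is a condensed article and the analysis plan is not shown. Estimators, covariates and intervals for secondary outcomes are commonly settled there. The section also names multilevel analysis for effectiveness, and the Effectiveness section describes measurement in both waves in all clinics. Pregnancy is a secondary outcome with no non-inferiority aim, and equal effectiveness is taken from a cited study as background.

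Much of this stands, and it rules out several stronger readings that a reader might infer.

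- *The baseline wave is discarded for secondary outcomes.* The article does not say so. It names baseline only for adherence and is silent on the rest.
- *A p-value would be the only evidence on pregnancy.* Pregnancy rates by arm and Kaplan-Meier curves are also planned.
- *A loss of pregnancies cannot be bounded.* The collected data allow an interval. The plan does not commit to one, and its width comes mainly from the sample size.
- *Precision is wasted.* That depends on an ICC and a between-wave correlation that the article does not give. At ICC 0.02 the gain is cancelled by the cost of the covariate.
- *The investigators will read non-significance as equality.* The article does not say this either.

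The reply does not remove the core. The article is not silent on method: it assigns a specific method to these outcomes, and that method is a descriptive contrast or a log-rank test with no stated allowance for clustering. The general mention of multilevel analysis is attached to no outcome, and the more specific sentences then name other methods.

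**Conclusion.** The point holds in limited form. For the secondary outcomes, the Data analysis section assigns methods that give no cluster-adjusted effect with a confidence interval, and it leaves the role of the baseline wave unstated.

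The firmest part is the ordinary log-rank test in a cluster-randomised trial. Its true error would be about 9% to 23% if the ICC for the time outcomes were 0.02 to 0.10. The article gives an ICC for adherence only, so the inflation could also be smaller.

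For pregnancy, an observed difference of zero would leave open a loss of about 9 to 15 points, given 225 couples per arm, a rate of 30-50% and an ICC of 0 to 0.1. A non-significant test therefore cannot support equal pregnancy chances. The document does not claim that it would.

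Baseline adjustment is the lesser argument, because its benefit runs from nothing to a moderate gain depending on assumed values. The primary outcome and the sample size figure are not affected by this point.

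**What to change.** Replace the descriptive sentence, and qualify the log-rank sentence, along these lines:

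- For each secondary outcome, the between-arm difference in the after wave (a hazard ratio for the two time outcomes) is estimated with a 95% confidence interval that accounts for clustering by clinic.
- Where the outcome is also measured at baseline, which covers at least the patient-related measures, the clinic's baseline-wave value is a covariate. A plain change from baseline is not used.
- The difference in pregnancy is reported with its 95% interval at a fixed horizon covered by the planned follow-up. A non-significant log-rank test is not interpreted as equal pregnancy chances.

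The horizon needs care. After-wave couples enter throughout the ten- to twelve-month intervention period, and the article states no follow-up length. A long horizon could require more follow-up than is planned. Pregnancies among couples who entered late in the baseline wave may also fall in the intervention period, so baseline-wave pregnancy should become a covariate only after that has been checked.

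The cost is revised wording and modest programming, with no new data if the horizon lies within planned follow-up. The downsides are a visibly wide pregnancy interval and about 5% in variance for the clinic-level covariate. The Trial status section says that baseline measurement is still under way, so the change can be fixed before after-wave data exist.

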## Outcome measures

### Primary outcome effectiveness

The primary outcome measure of the proposed study for effectiveness will be the guideline adherence rate on TEM: the percentage of couples that are eligible for TEM (couples with mild or unexplained infertility with a prognosis of >30% of natural conception within one year) who actually agree upon the expectant management period of at least six months after the initial fertility assessment is concluded.

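### Kaplan-Meier for time to start of fertility treatment: if natural conceptions are censored, the share treated is overstated in both arms, at 12 months by more in the arm that waits longer; the log-rank also ignores clinic

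*Protocol article*

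**What the plan says.** In the protocol article, Secondary outcomes effectiveness lists, as treatment-related measures, "time to the start of fertility treatment and the number and types of fertility treatments that the couples received". Data analysis fixes the method: "time to pregnancy and time to start fertility treatment will be analyzed using Kaplan Meier analysis with log-rank test". The same section announces multilevel analysis in general terms, but the test it names for this outcome is a single-level one.

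Three other sections bear on the choice:
- Study population/participants: eligible couples must "have a good prognosis (>30%) according to Hunault’s prediction model". Primary outcome effectiveness repeats the threshold: "prognosis of >30% of natural conception within one year".
- Primary outcome effectiveness: adherent couples are those "who actually agree upon the expectant management period of at least six months after the initial fertility assessment is concluded".
- Sample size: "The expected adherence to TEM in the control arm is estimated based on previous studies at 60" per cent, and the target is "To increase this to 80% with an intra-class correlation (ICC) of 0.1, alpha at 5%, comparing two strategies".

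The article does not say what happens in this analysis to a couple who conceive before any treatment.

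**The concern.** A couple who conceive naturally generally no longer need treatment. In this population that is a common outcome, and a longer wait exposes more couples to it. Kaplan-Meier conventionally censors such couples, which treats them as if they would have gone on to start treatment at the rate of those still trying. 1-KM then describes a setting in which nobody conceives naturally. It does not give the share of couples who actually receive treatment.

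That share matters here. The Background motivates the trial by overtreatment, and the Discussion expects fewer insemination and IVF/ICSI cycles. Part of the expected benefit is that couples who wait conceive and never need treatment, and a curve that censors conception removes that part from view.

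A second, separate issue is that an ordinary log-rank test treats couples as independent, although clinics are randomised and the plan itself assumes correlation within clinics.

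**Working it through.** **1. The plan's own figure.** Sample size states: "we estimate that with 25 clusters we would need a total sample size of 450 patients". Assume two-sided 5%, 80% power (not stated) and equal allocation. Comparing 60% with 80% needs 82 per arm, or 164 in all. Mean cluster size is 450/25 = 18, so the design effect is 1 + (18 - 1) x 0.1 = 2.7. Then 164 x 2.7 = 443, close to the stated 450 (power at 450 is about 81%). The plan's inputs are therefore coherent and can be carried over.

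**2. Inputs for time to treatment.**
- From the article: adherence a = 0.60 (control) and 0.80 (intervention); a wait of at least six months in adherent couples; conception above 30% per year.
- Assumed: conception q = 30% or 40% per year at a constant hazard, independent of treatment timing; non-adherent couples start evenly over months 0-3; adherent couples start evenly over months 6-9, 6-12 or 6-18; a 12-month horizon (follow-up for this outcome is not stated).

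**3. Formulas.** Monthly conception hazard: h = -ln(1 - q)/12. For couples who would start evenly between months s and e, by month t (with s < t):
- proportion started if nobody conceived, which 1-KM estimates when conceptions are censored: (min(e,t) - s)/(e - s)
- proportion actually treated (cumulative incidence): [exp(-hs) - exp(-h min(e,t))] / [h(e - s)]

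Each arm is (1 - a) x non-adherent + a x adherent.

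**4. One case in full** (q = 30%, adherent starts in months 6-18, t = 12). h = 0.3567/12 = 0.0297.
- Non-adherent: 1-KM 1.000; treated (1 - exp(-0.0892))/0.0892 = 0.957.
- Adherent: 1-KM 6/12 = 0.500; treated (0.8367 - 0.7000)/0.3567 = 0.383.
- Control: 1-KM 0.4 + 0.6 x 0.500 = 70.0%; treated 0.4 x 0.957 + 0.6 x 0.383 = 61.3%; overstated by 8.7 points.
- Intervention: 1-KM 0.2 + 0.8 x 0.500 = 60.0%; treated 0.2 x 0.957 + 0.8 x 0.383 = 49.8%; overstated by 10.2 points.
- Difference between arms: 10.0 points on the Kaplan-Meier scale, 61.3 - 49.8 = 11.5 in truth.

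**5. All cases at 12 months** (1-KM / treated, overstatement in points):

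| q | adherent start | control | intervention |
|---|---|---|---|
| 30% | 6-9 | 100.0 / 86.3, 13.7 | 100.0 / 83.2, 16.8 |
| 30% | 6-12 | 100.0 / 84.2, 15.8 | 100.0 / 80.4, 19.6 |
| 30% | 6-18 | 70.0 / 61.3, 8.7 | 60.0 / 49.8, 10.2 |
| 40% | 6-9 | 100.0 / 81.2, 18.8 | 100.0 / 76.9, 23.1 |
| 40% | 6-12 | 100.0 / 78.6, 21.4 | 100.0 / 73.5, 26.5 |
| 40% | 6-18 | 70.0 / 58.1, 11.9 | 60.0 / 46.1, 13.9 |

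The range is 8.7-21.4 points in control and 10.2-26.5 in intervention. In the 6-9 and 6-12 rows Kaplan-Meier shows no 12-month difference, although 3.1 to 5.1 points more control couples were treated.

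**6. Earlier horizons and wider assumptions.** At six months the overstatement is 1.7-2.4 points in control and 0.9-1.2 in intervention. Adding q = 50% and non-adherent starts over months 0-6 gives 18 scenarios. At 12 months the later-treating arm is overstated more in all 18; at 9 months it is overstated more in points in 15 of 18, and relatively in all.

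**7. Clustering.** If the ICC of 0.1 held for this outcome, the design effect of 2.7 would turn a nominal critical value of 1.96 into 1.96/sqrt(2.7) = 1.19 on the correct scale. Two-sided, that is a type I error of about 23%.

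**The case against.** **The censoring rule is not written down.** If couples who conceive are kept in the risk set as untreated to the end of follow-up, 1-KM equals the cumulative incidence and the bias disappears. An article can leave such detail to a fuller document. This stands as a condition on the finding. But the article does commit to a named method whose conventional use censors these couples, and it names no competing-event method.

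**The log-rank test is not invalidated by the competing event.** With pregnancy censored it tests the cause-specific hazard of starting treatment, which is also what a cause-specific Cox model addresses. This stands: clustering aside, the fault lies in reading the curve as a proportion treated. The article does not say the curve will be read that way, and it summarises treatment-related measures descriptively as well.

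**A reader might infer that the bias is larger in the earlier-treating arm and so exaggerates the strategy's effect.** Constant hazards can give that in absolute points. With 35% conception per year, 1-KM values of 60% and 30% correspond to 50.3% and 24.7% treated, so a 30-point gap is really 25.6 points. But the 60% and 30% are not in the article, and constant hazards ignore the six-month wait. Even there the relative overstatement is larger in the lower-treating arm (0.60/0.503 = 1.19 against 0.30/0.2469 = 1.22). With the plan's own adherence and wait, the direction at 12 months reverses.

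**A reader might also call this the main secondary outcome.** The article does not rank its secondary outcomes.

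**Conception does not always end the need for treatment.** Miscarriage and extra-uterine pregnancy are recorded outcomes, and treatment may follow them. This stands, and the event definition should cover it.

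**Multilevel analysis is announced.** That is so in general terms, but the test specified for this outcome does not use it.

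**Conclusion.** The concern holds, provided couples who conceive are censored. 1-KM then overstates the proportion treated in both arms, and unequally: at 12 months by about 9-21 points in control and 10-27 in intervention, against about 1-2 points at six months. The likely effect at 12 months is to hide treatment avoided through natural conception. The documents do not support the claim that the curves flatter the strategy.

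The existence of the bias follows from the method and the eligibility rule. Its size depends on the assumed conception rate, start times and horizon, and on every couple who does not conceive eventually starting treatment, which is why 1-KM reaches 100% in some rows. The 23% type I error depends on the primary outcome's ICC carrying over to this outcome.

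**What to change.** In Data analysis, replace the Kaplan-Meier and log-rank wording for time to start of treatment with the following:
- Estimate the cumulative incidence of treatment start by the Aalen-Johansen method, with pregnancy before treatment as the competing event. Report the between-arm difference at 6 and 12 months.
- Compare arms with a cause-specific Cox model using clinic-robust standard errors or a clinic frailty.
- State how couples who conceive are handled, including those whose pregnancy ends in loss.
- Account for clinic clustering in the time-to-pregnancy comparison as well.

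The cost is small. Treatment and pregnancy outcomes, including time to pregnancy, are already planned from the medical records, so no new data item should be needed. The change is analysis wording plus some extra analysis work, possibly in software other than the SPSS 16.0 that the article names. According to Trial status, the baseline measurement was still under way.
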